# Entry and exit of criteria

## Inclusion criteria

All the subjects who meet all of the following conditions are enrolled in this experiment:

Inclusion criteria:

1. Male and female aged 18 to 70 years old;

2. BMI within 18.5-26kg/m2;

3. Mild to moderate essential hypertension according to the diagnostic criteria of China (2005);

4. The mean seated blood pressure after 2-week washout period with placebo (the blood pressure should be detected 3 times every 2 minutes after 5-minute resting in sitting position and then take the mean value) should be 140mmHg ≤SBP<180mmHg and 90mmHg ≤DBP< 110mmHg;

5. Able and willing to provide signed informed consent.

## Exclusion criteria

The subjects meeting one of the following conditions will not be selected in the test:

1. Having been diagnosed or suspected as secondary hypertension;

2. The difference of systolic blood pressure in seated place measured for three consecutive times is greater than 20 mmHg, and the difference of diastolic pressure is greater than 10 mmHg;

3. Sick sinus syndrome, II~III atrial ventricular block, atrial flutter, atrial fibrillation, or other malignant arrhythmia;

4. Aneurysm in conducting artery or dissecting aneurysm, percutaneous tranluminal coronary angioplasty (PTCA) or other cardiac surgery;

5. Unstable angina pectoris, acute myocardial infarction, cardiac failure, and cerebral accidents within recent 6 months;

6. Asthma or moderate to severe chronic obstructive lung disease;

7. Uncontrolled diabetes, FBG≥11mmol/L or with complications (degenerative nephritis and peripheral neuropathy);

8. Renal arterial stenosis;

9. Renal inadequacy ( Cr>1.5×ULN (the upper limit of the normal range);

10. Serious hepatopathy or hepatic inadequacy (ALT, AST or TBIL> 2×ULN);

11. Electrolyte disturbances (blood potassium or sodium abnormality);

12. Subjects with lower blood volume;

13. Female subjects with pregnancy or in lactation;

14. Subjects with drug or alcohol dependence;

15. Concomitant treatment with other drugs which will affect the blood pressure;

16. Subjects with resistant hypertension;

17. Allergy to any ingredient in the study;

18. attend other clinical trail within 3 month;

19. Suspected as white overcoat hypertension according to the judgment of investigators;

20. Subjects are thought unsuitable for the study by investigators.

## Exiting criteria

The subjects can withdraw from the experiment at any time. The exiting reasons are mainly as follows:

1. Withdrawal the study under patients willing will;

2. Occurrence of serious adverse events or intolerable adverse events;

3. Seated SBP ≥ 180 mmHg or seated diastolic blood pressure ≥ 110mmHg during the study;

4. Serious violations of inclusion and exclusion criteria;

5. Poor compliance to the protocal;

6. Lost of follow-up;

7. Other reasonsFor subjects withdrew from the experiment, the researchers should ask whether there is occurrence of any adverse event, and request the completion of the last interview of the participants as far as possible. Laboratory tests should be conducted and adverse events are recorded, and adverse events should be tracked.

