| **Statistical analysis** | **Estimation of sample sizes:**  This is a superior efficacy test study. The efficiency test was conducted on the main therapeutic effect index. Setting bilateral α = 0.05, *β* = 0.20, and the standard deviation SD = 7.8 mmHg, the difference of the antihypertensive effect in the two groups were detected as *D* = 3 mmHg. The distribution ratio of the patient cases in the two groups was 1:1. The estimated minimum sample size was 108 pairs. Taking into account of the factors such as dropping, the present research plan included 260 cases into the two groups with 130 cases of patients in the experiment group and the control group, respectively.  **Statistical analysis of the data set:**  Statistical analysis was conducted by using the full analysis set, per-protocol population set and safety data set. The quality control was strictly carried out in the whole process of the data statistics to ensure the authenticity of the assessment of data.  Full analysis set (Full analysis set, FAS): according to the fundamental principle of intention to treat (ITT), all the randomly enrolled subjects with more than one medication administration record and effective evaluation were included in the full analysis set. When selecting full analysis set for analysis, the latest observation LOCF (LOCF) estimation method was adopted for the estimation of the missing values. Full analysis set is the main effectiveness method for the evaluation of population in the present study.  The Per-Protocol set (PPS): PPS included all the subjects with completed prescribed treatment protocal or no serious violations of tests. The exact definition of the serious violations of the scheme will ultimately determined in the data auditing, which generally included the following situations (but they are not limited to these cases): Not meeting the inclusion criteria, having interference treatment after being selected, poor compliance, interview beyond the time window. PP set is a secondary analysis of the crowds of the effectiveness, but if the results were inconsistent with the full analysis set, detailed analysis should be done on the inconsistent results.  Safety data set (Safety Set, SS): the definition of safety data set was the subjects that at least received one time drug treatment.  **Statistical analysis method:**  Statistical analysis was conducted by using the SAS9.13 statistical analysis software for calculation. Quantitative description of the parameters included the calculation of mean, standard deviation, median, minimum value and maximum value. The description of the classified index employed the case number and percentage of the cases.  Descriptive statistics were conducted on the completion of the study. The comparison among groups was conducted on the demographic and baseline characteristics to analyze the equilibrium between groups.  Analysis of the main outcome measures: the main efficacy index will use the test of superiority. In addition, the dereasee value os DBP of each subject after treatment of 8 weeks will also be calculated, and descriptions in each group were done (mean, standard deviation, median, minimum, maximum). Comparisons between groups used analysis of variance considering center effect.  Analysis of the secondary outcome indicators: the center effect was not considered in principle. Comparisons between groups employed the variance analysis, chi-square test or nonparametric statistical method.  Analysis of the safety evaluation: parameters of safety evaluation included adverse events/ adverse drug reaction (ADR)/important adverse events or serious adverse events, physical examination and laboratory examination and a 12-lead electrocardiogram. Detailed description was conducted on the cases of adverse events during the test. The incidence rates of the adverse events between the two groups were summarized and compared. The indexes of laboratory examination were statistically described. The difference between two groups was compared when it was necessary. A detailed description of the laboratory indexes and normal cases before treatments was conducted.  This study did not conduct interim analysis. |

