**3）Regulations of breaking blinding**

At the same time of encoding the research drugs, an emergency message was prepared for each drug number by the biostatisticians producing blinding end. The exact group of the number of the drug was sealed in the letter envelope. The emergency letters accompanied with the drugs of the corresponding numbers were distributed to various clinical research units by the researchers in charge of the unit. Emergency letter can only be used for emergency. They will be unsealed only the medication conditions should be understood and the treatment measures should be taken such as serious adverse events.

If the emergency envelope is opened, the exposing blind time, date and the reasons must be recorded on the envelope and the name of the people uncovering the blind should be signed off, and the Hangzhou Tigermed Co. Ltd. (CRO) company should be informed immediately. Once emergency letter is opened, the case is treated as the shedding case.

At the end of the study, all the emergency letters (opened or not) must be called back together with the completed case report form. The emergency letters should be checked when inspector visits each time to determine the envelope is not opened freely, or the number of envelops that have been opened is recorded clearly.

Blind can not be broken after double-blind treatment of 8 weeks. All participants will take part in a safety observation period of 56 weeks under blind states. The time of blind exposure is determined according to the requirements of the data statistics and analysis procedures of the double-blind treatments.

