### The unplanned outside interview

If subjects need extra interviews or early exiting test, the measures having been taken by researchers (including laboratory test results) should be recorded on the original case history and the unplanned interview table in the case report table.

In addition, when the subjects exit the tests early before the interview 5 or enter the safety observation period early to end the safety observation period, the following aspects should be done as far as possible:

- - Physical examination: physical examination of all body systems;
  - Resting sitting blood pressure and heart rate were measured: the measurement method is as the same as that of the screening period;
  - Laboratory and auxiliary examination: including urine pregnancy test (limited to women of childbearing age), whole blood test, urine routine test test, liver function, renal function, fasting blood glucose, blood lipid, blood electrolyte and a 12-lead electrocardiogram;
  - Recovery of all the remaining study drug and counting;
  - Recovery, transcfer and recording of the diary cards of the subjects (only applicable to the subjects during the double-blind study);
  - Recording adverse events and concomitant treatments.

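### Sections 4.3 and 5.2.2 do not separate stopping study drug from leaving the study, so some randomised patients lose a week-8 pressure that could have been measured

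*Protocol*

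**What the plan says.** **Exit.** Section 4.3, repeated in the protocol summary, introduces its list with "The exiting reasons are mainly as follows". Item 4 is "Serious violations of inclusion and exclusion criteria" and item 5 is "Poor compliance to the protocal". They stand beside withdrawal by the patient and loss to follow-up. The section gives no compliance threshold.

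**Unblinding.** Section 5.2.2 states: "Once emergency letter is opened, the case is treated as the shedding case". Section 3 uses the same term for the 20% loss between 216 evaluable and 260 enrolled patients.

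**After exit.** Section 4.3 asks sites to "request the completion of the last interview of the participants as far as possible". Section 5.3.8 adds an early-exit work-up, also where possible, which includes: "Resting sitting blood pressure and heart rate were measured: the measurement method is as the same as that of the screening period". Neither section schedules a reading at week 8 for a patient who has left.

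**Analysis sets.** The summary defines the FAS, the main efficacy set, as "according to the fundamental principle of intention to treat (ITT), all the randomly enrolled subjects with more than one medication administration record and effective evaluation". Missing values in it are filled by LOCF; section 11.2 says only that LOCF may be used. Section 7.3 gives compliance limits of 80% and 120% and one consequence of breaching them: the patient does not enter the PPS. The summary and section 11.2 likewise list ineligibility and poor compliance as PPS exclusions.

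**The concern.** The primary outcome is the change in trough seated diastolic pressure to week 8. A patient who takes tablets irregularly, proves ineligible after randomisation or has an emergency letter opened can usually still be measured at week 8. If the site treats the event as an exit, the trial gives up that measurement itself.

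Compliance and unblinding arise after randomisation and may depend on the arm, for example through poor control on placebo or side effects on drug. Missing values produced this way can be informative, and they fall in the set that is said to follow intention to treat. Section 4.3 sets no threshold, so site judgement can decide whether the primary value of a poor complier is observed or imputed.

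A later analysis plan can choose how to handle missing values. It cannot recover pressures that were never taken, so the point belongs in the protocol.

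**Working it through.** **1. The plan's own figure.** The section 11.1 inputs are D = 3 mmHg, SD = 7.8 mmHg, 108 per arm and one-sided alpha 0.025. The noncentrality is 3 / (7.8 × √(2/108)) = 3 / 1.061 = 2.83 with 214 degrees of freedom. The power is 0.803, against 0.80229 stated. The sample size reproduces and is not in question.

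**2. The rules side by side.**

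| Patient | Read from 4.3 / 5.2.2 | Read from 7.3, 11.2 and summary |
| --- | --- | --- |
| Poor complier | May exit; last reading at exit; week 8 filled by LOCF | Continues; observed week-8 value in FAS; out of PPS |
| Found ineligible after randomisation | May exit; same result | Settled at data review; observed value in FAS; out of PPS |
| Emergency-unblinded | Drop-out; use of later readings not stated | Not named |

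The first two rows give different primary data for the same patient, and no text says which rule prevails. In any row, a patient with no efficacy evaluation leaves the FAS and is not imputed.

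**3. What the documents say about numbers.** In the earlier phase II trial, 34/283 = 12.0% dropped out and 7/283 = 2.5% were excluded, together 41/283 = 14.5%. Its FAS held 279, so 283 − 279 = 4 patients were outside it. At least 34 − 4 = 30 drop-outs were therefore inside, or 30/279 = 10.8%. Drop-outs can thus be a material part of the primary set. The present trial allows 20%, and 0.20 × 130 = 26 per arm. All these counts cover every cause. The share due to the three events here is not given.

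**4. Illustration of dilution (assumed inputs).** Let x be the share of each arm that exits and f the fraction of the 3 mmHg difference that the carried-forward values still show. The expected difference is 3 × (1 − x(1 − f)). Power is for 130 per arm in the FAS and SD 7.8.

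| x | Difference, f = 0 to 1 | Power, f = 0 to 1 |
| --- | --- | --- |
| 5% | 2.85 to 3.00 mmHg | 0.835 to 0.871 |
| 12% | 2.64 to 3.00 mmHg | 0.776 to 0.871 |
| 20% | 2.40 to 3.00 mmHg | 0.695 to 0.871 |

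The 12% and 20% rows use all-cause losses, so they are outer limits for these three reasons.

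**5. Illustration of unequal exits (assumed inputs).** Suppose the carried-forward value is wrong by the same amount in both arms. Then bias = (difference in exit proportion) × (that error). A 5-point difference and an error of 3 to 5 mmHg give 0.05 × 3 = 0.15 to 0.05 × 5 = 0.25 mmHg. That is 5% to 8% of the 3 mmHg target. The standard error is 7.8 × √(2/130) = 0.97 mmHg, so the bias is 0.16 to 0.26 of it. A 10-point difference doubles these figures. Neither the imbalance nor the error has a source in the protocol.

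**The case against.** A reader might infer that measured week-8 pressures of these patients are thrown away. The documents do not say so. LOCF is for missing values, so an observed week-8 pressure would be used, and a poor complier or ineligible patient who reaches week 8 stays in the FAS under section 7.3, section 11.2 and the summary. The loss concerns only those who exit earlier.

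A reader might also infer that all three groups must be removed as drop-outs. Only the emergency-unblinded are expressly so classed. The list in section 4.3 describes the main reasons for leaving and is not worded as an obligation.

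Three further objections stand in part:

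- The early-exit work-up includes seated pressure by the standard method, so the value carried forward may be a recent one. It is still a reading at exit and not at week 8.
- Ineligibility is mostly fixed before randomisation. With blinding intact there is no evident reason why its discovery should differ by arm. The argument for arm-dependent loss rests on compliance and unblinding.
- Later readings have weaknesses of their own. Off drug there is no pressure 23 to 26 hours after a dose, as section 8.1 requires. Another antihypertensive may have been started. Appendix 2 specifies a mercury sphygmomanometer read by ear, so readings after unblinding may be influenced by the observer. This does not justify failing to collect the readings, but it does mean that their use must be qualified.

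**Conclusion.** The point holds as a defect of design wording. Leaving study drug and leaving the study are not separated, no week-8 reading is planned after exit, and the exit rule and the PPS-only rule for poor compliance and ineligibility are not reconciled. For affected patients who leave before week 8, the primary value is imputed or the patient drops out of the FAS, against the principle that the set claims to follow.

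The size is unknown. The documents fix neither the number of exits for these reasons nor the direction or magnitude of any bias. The figures in the illustrations rest on assumed inputs, show scale only and should not be quoted as estimates for this trial. This is a cheap improvement to the protocol. It is not evidence that the primary result would be wrong.

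**What to change.** Reconcile section 4.3 (with the matching summary list) and section 5.2.2 with section 7.3, section 11.2 and the summary's definitions of the analysis sets:

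- State that poor compliance, an eligibility violation found later, or emergency unblinding does not by itself end blood pressure follow-up.
- Keep the scheduled week-4 and week-8 blood pressure visits for these patients unless consent is withdrawn.
- Keep observed readings in the FAS and apply these violations to the PPS only.
- Flag readings taken off study drug, after another antihypertensive or after unblinding. Report a sensitivity analysis without them that uses the exit-visit value instead.

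Whether study drug stops is left to the existing clinical rules.

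**Cost.** The change is wording in a few sections, a flag in the data and one extra analysis; the visits are already in the schedule. The downside is that some readings will be off drug, not true trough values or affected by other treatment, and may dilute or blur the effect. The sensitivity analysis would show how much.

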# Research design

## Research types and design principles

The study design is a randomized, double-blind, placebo-controlled, multi-center and phase I clinical trial.

After selection of the qualified 260 subjects, ther are randomly assigned to the following one of two groups at a ratio of 1:1:

The test group A: Allisartan Isoproxil tablet of 240 mg (130 cases)

The control group B: Allisartan Isoproxil placebo tablet of 240 mg (130 cases)

According to the clinical evaluation principles of anti-hypertensive drug E12A of the International Conference on Harmonization of technical requirements for registration of pharmaceuticals for human use (ICH), the middle and low risk patients with primary hypertension with ages of 18 ~ 70 years old are selected as the research population; Based on the effects of the different doses of the research drug on blood pressure that has been conducted in II stage and the exploration of the relationship between dose and effect, to confirm the absolute antihypertensive efficacy of the research drugs, the present study selects clinical objective only using fixed dose of Allisartan Isoproxil of 240 mg, and the parallel controlled study is conducted using the corresponding placebo; The treatment period is set as 8 weeks (in the placebo-controlled study, the maximum application time of the placebo is not more than 10 weeks) to observe the comparative efficacy and safety of the research drugs and placebo. At the same time, in order to observe the long term efficacy and safety of the research drugs, all subjects will participate safety observation period of 56 weeks voluntarily after they finish the double-blind treatment of 8 weeks, during which each subject will receive daily treatment of 240 mg Allisartan Isoproxil tablet once a day.

## Randomization and blinding

### Randomized method

The qualified subjects are selected. Drug number will be distributed randomly and the drugs corresponding to the drug number are given by the research doctor according to the grouping of each subject in order from small to large, which cannot be arbitrarily or intentionally selected. The number of the drug is maintained stable throughout the test process of the subject.

### Rules of breaking blinding of the randomized double-blind trial

**1）Blinding and preservation of blinding sheet**

Package of software was analyzed in computer by the biostatistician independent of the implementation of the data management and statistical analysis in the present study by using the SAS 9.13. The random encoding was produced by using the stochastic approach in the experiment group and the control group according to a ratio of 1:1. The length of the selected block and the initial seed parameters of the random number were sealed in the bottom of the blind area together as confidential data. The drugs were encoded according to thses random number under the surveillance of the personnel unrelated to the present test. The drugs were used by various clinical research centers according to the distributed number of the drugs and the grouping sequence of the cases. The blind end of two copies were sealed and stored in the sponsor’s department and the national drug clinical trial institution Office, the Third Xiangya Hospital of Central South University, the blind end should not be opened during the test.

**2）Enforcement of the blind method**

This study is a double-blind design. The extrinsic features of the research drug and placebo pills are exactly the same. The quantity of the research drug and the extrinsic features of the research drug taken by each subject are completely the same. In order to ensure that the batch number of the drugs used by each subject can be traced the source and ensure the blind test, the batch number of the research drug corresponding to each subject was recorded in the blind end when the research drugs were encoded blindly.

**3）Regulations of breaking blinding**

At the same time of encoding the research drugs, an emergency message was prepared for each drug number by the biostatisticians producing blinding end. The exact group of the number of the drug was sealed in the letter envelope. The emergency letters accompanied with the drugs of the corresponding numbers were distributed to various clinical research units by the researchers in charge of the unit. Emergency letter can only be used for emergency. They will be unsealed only the medication conditions should be understood and the treatment measures should be taken such as serious adverse events.

If the emergency envelope is opened, the exposing blind time, date and the reasons must be recorded on the envelope and the name of the people uncovering the blind should be signed off, and the Hangzhou Tigermed Co. Ltd. (CRO) company should be informed immediately. Once emergency letter is opened, the case is treated as the shedding case.

At the end of the study, all the emergency letters (opened or not) must be called back together with the completed case report form. The emergency letters should be checked when inspector visits each time to determine the envelope is not opened freely, or the number of envelops that have been opened is recorded clearly.

Blind can not be broken after double-blind treatment of 8 weeks. All participants will take part in a safety observation period of 56 weeks under blind states. The time of blind exposure is determined according to the requirements of the data statistics and analysis procedures of the double-blind treatments.

